**PRIMARY OUTCOME:**			
**General cognitive assessment**	✓	✓	✓
•Montreal cognitive assessment (MoCA) (28)			
**Memory**	✓		✓
•The Digit span and the Corsi span tasks (backward and forward) (29)			
•Free and Cued Selective Reminding Test (FCSRT) (30)	✓		✓
•Recall of rey's figure (31)	✓	✓	✓
**Attention and executive functions**	✓		✓
•The modified card sorting Test, short version (MCST) (32)			
•The Trial Making Test (TMT) (33)	✓		✓
•Stroop test, short version (34)	✓	✓	✓
**Visuospatial/constructional ability**	✓	✓	✓
•Copy of rey's figure (31)			
**Language**	✓	✓	✓
•Semantic fluency (35)			
•Fonemic fluency (36)	✓	✓	✓
**SECONDARY OUTCOMES:**			
**Activities of daily living inventory**	✓	✓	✓
•The Activities of Daily Living Inventory (ADCS-ADL) (37)			
**Depression symptoms**	✓	✓	✓
•The center for Epidemiological Studies Depression scale (CES-D) (38)			
**Health status**	✓		✓
•The 36-Item Short Form Survey (SF-36) (39)			
**Cognitive reserve**	✓		
•The cognitive Reserve Index questionnaire (CRIq) (40)			
**Physical activity level**	✓	✓	✓
•The short Physcal performance battery (SPPB) (41)			
•The Harvard Alumni Activity Survey (HAAS) (42)	✓		✓
•The International Physical Activity Questionnaire (IPAQ) (43)	✓		✓

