### Participants' Evaluation

Participants will be assessed through an extensive evaluation including cognitive functioning, behavioral, functional and perceived quality of life measures with the following tests (Table 2):
The Montreal cognitive assessment [MoCA; (28)], which represents a sensitive tool in persons with MCI for a general cognitive assessment;The Digit span and the Corsi span tasks (backward and forward) (29), to assess both verbal and visuo-spatial short-term memory and working memory;The Free and Cued Selective Reminding Test [FCSRT; (30)] -Delayed Free Recall (DFR) and Immediate Free Recall (IFR) for verbal episodic memory evaluation;The Rey Complex Figure Test, copy and delayed recall [RCFT; (31)], to evaluate constructional skills, visuographic memory and some aspects of planning and executive function;The modified card sorting Test, short version [MCST; (32)] for the assessment of executive functions;The Trail Making Test [TMT; (33)] for the assessment of attention and -executive functions;The Stroop test, short version (34), to assess selective attention, cognitive flexibility and sensitivity to interference;The Semantic and Fonemic fluencies (35, 36) or the assessment of language skills;The Activities of Daily Living Inventory [ADCS/ADL; (37)] to assess patient's performance in the basic and instrumental activities of daily living.The center for Epidemiological Studies Depression scale [CES-D; (38)] to evaluate both the presence and the entity of depressive symptoms;The 36-Item Short Form Survey [SF-36; (39)] to assess the subjective perceived quality of live;The cognitive Reserve Index questionnaire [CRIq; (40)] for the evaluation of the cognitive reserve;The Short physical performance battery [SPPB; (41)], to measure functional status and physical performance;The Harvard Alumni Activity Survey [HAAS; (42)], to assess physical activity level;The International Physical Activity Questionnaire – Short Form [IPAQ; (43)], for health related physical activity evaluation.

**Table 2 T2:** Evaluation battery during the proposed trial.

**Outcome measures**	***T_0***	***T_1***	***T_2***

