### Outcomes Measures

As the aim of this program will be to involve the participants in multidimensional activities to counteract cognitive decline, the primary outcome of this study will be the changes of cognitive domains evaluated (such as general cognitive assessment, memory, attention, and executive functions, visuospatial/constructional ability, and language) of the whole sample through a comprehensive neuropsychological assessment at T_0 and at T_2 (see Table 2 for a detailed list of the used neuropsychological tools). Together with the cognitive level, the following secondary outcomes will be evaluated in the whole sample at T_0 and T_2: independence, presence of depressive symptoms, quality of life and physical activity level through scales and actigraphic data (see Table 2 for the used questionnaires). In addition, the primary and secondary outcomes will be evaluated in the treatment group before and after the tele-rehabilitation program using a reduced battery of tests (see Table 2).

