### Statistical Analyses

Statistical analysis on outcome measures will be conducted using SPSS version 24 (SPSS Inc, Chicago, IL). Baseline differences between groups will be tested by the independent-samples *t*-test for parametric data and the Mann-Whitney *U*-test for non-parametric data. According to data normality, a statistical test for independent samples will be performed to look at significant changes in primary and secondary outcome measures between control and treatment groups. Moreover, a statistical test for paired sample will be used to investigate the presence of significant changes in the treatment group cognitive and physical parameters before and after the tele-rehabilitation program. An alpha level of ≤ 0.05 will be considered as significant.

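### The Cognitive Reserve Index is labelled a secondary outcome but measured only at T0, so the planned test of change cannot be applied to it; it belongs with the baseline data

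*Protocol article*

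**What the plan says.** Three parts of the protocol article bear on this point.

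- **Table 2.** Under the heading "SECONDARY OUTCOMES" there is a row for cognitive reserve, assessed with "The cognitive Reserve Index questionnaire (CRIq) (40"). Its only tick is at T0; T1 and T2 are blank. The Participants' Evaluation section says only that the instrument is "for the evaluation of the cognitive reserve".
- **Outcomes Measures.** This section states that "the following secondary outcomes will be evaluated in the whole sample at T_0 and T_2", and names them as "independence, presence of depressive symptoms, quality of life and physical activity level through scales and actigraphic data". Cognitive reserve is not in the list. The reader is sent to Table 2 for the questionnaires.
- **Statistical Analyses.** An independent-samples test, chosen according to normality, will be used "to look at significant changes in primary and secondary outcome measures between control and treatment groups". A paired test covers before-and-after changes in the treatment group. A separate sentence provides for testing baseline differences between groups. No covariate is named.

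The Study Design section places the T0 assessment before random assignment.

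**The concern.** A secondary outcome needs at least one value after randomisation. This one has none, so the analysis that the article states for secondary outcomes has nothing to work on. The table and the text also disagree on which measures are secondary outcomes and when they are assessed. The article commits to CONSORT reporting, so a reader of the results would look for a finding on every declared secondary outcome, and for this one no such finding can exist.

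A value taken before randomisation can serve as a baseline characteristic or a covariate. The between-arm test that the article describes is unadjusted, so as stated it makes no use of this value, or of the T0 cognitive scores other than through the change.

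**Working it through.** **Schedule against definition.** Table 2 has seven instruments under secondary outcomes.

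| Instrument | T0 | T1 | T2 | T0-to-T2 change available? |
|---|---|---|---|---|
| ADCS-ADL | yes | yes | yes | yes |
| CES-D | yes | yes | yes | yes |
| SF-36 | yes | no | yes | yes |
| CRIq | yes | no | no | **no** |
| SPPB | yes | yes | yes | yes |
| HAAS | yes | no | yes | yes |
| IPAQ | yes | no | yes | yes |

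Six of the seven satisfy the T0-and-T2 rule in Outcomes Measures. CRIq is the only exception, with 1 scheduled assessment at T0, 0 at T1 and 0 at T2.

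**Schedule against analysis.**

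- Between-arm test of change: needs T0 and T2. Not possible.
- Paired test in the treatment group: needs T0 and T1. Not possible.
- Baseline comparison between groups: needs T0 only. Possible, but because T0 precedes randomisation, any difference is chance imbalance and not an effect of treatment.

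**What CRIq could add as a covariate.** The article gives no correlation between CRIq and any cognitive score, so this part rests on an assumption.

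- Inputs: 60 participants (Sample Size), all taken as analysed at T2. Partial correlation *r* of CRIq with the T2 score, given arm and the score's own T0 value: assumed 0 to 0.3.
- Residual variance is multiplied by 1 − *r*².
- Cost of estimating one more coefficient: two arm means and the T0 score leave 60 − 3 = 57 residual degrees of freedom, and adding CRIq leaves 56. The variance of the arm comparison rises by roughly 1/56 = 1.8%, a factor of 1.018.
- Effective sample size relative to the same model without CRIq = 1 / [(1 − *r*²) × 1.018].

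| Assumed *r* | 1 − *r*² | × 1.018 | Effective sample size |
|---|---|---|---|
| 0 | 1.00 | 1.018 | 0.98 (loss of about 2%) |
| 0.1 | 0.99 | 1.008 | 0.99 (loss of about 1%) |
| 0.2 | 0.96 | 0.977 | 1.02 (gain of about 2%) |
| 0.3 | 0.91 | 0.926 | 1.08 (gain of about 8%) |

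Break-even is where (1 − *r*²) × 57/56 = 1, so *r*² = 1/57 = 0.0175 and *r* is about 0.13. On 60 participants the range runs from about 1 fewer (60 × 0.02 = 1.2) to about 5 more (60 × 0.08 = 4.8).

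**The case against.** The strongest reply is that this is a heading slip which the text already resolves. Outcomes Measures omits cognitive reserve, Table 2 also serves as the assessment schedule, and a lone T0 tick among six instruments with T0 and T2 looks like a deliberate baseline measure placed under the wrong heading. That is probably the intention, and it limits the seriousness. It does not remove the inconsistency, because Outcomes Measures relies on Table 2 to complete its definition.

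Three stronger readings are tempting, and the article does not support them.

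- *A baseline difference in CRIq would be reported as a treatment effect.* Statistical Analyses deals with baseline differences in a sentence of its own, apart from the sentence on changes. A T0-only value falls under the former.
- *CRIq is a covariate left unused.* It can enter the planned baseline comparison and describe the sample. A covariate list is also commonly left to a full analysis plan, which is not shown.
- *CRIq is prognostic, so precision is being lost.* No passage says so. A trait related to the level of cognition may be only weakly related to its later course once the T0 score is in the model. The gain may therefore be nil or slightly negative.

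Adjustment remains worth raising because the article does more than stay silent. It states a particular between-arm method, and that method is unadjusted.

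**Conclusion.** The inconsistency is certain and rests on no assumed number: CRIq is declared a secondary outcome, breaks the article's own timing rule for secondary outcomes, and cannot be analysed by the method given for them. It is minor. Reclassifying it alone changes no result.

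The case for adjustment is a modest improvement and not the repair of an error. The part due to CRIq lies between a loss of about 2% and a net gain of about 8% in effective sample size. This assumes a partial correlation of 0 to 0.3 and complete T2 data on 60 participants, and the gain turns positive only above a correlation of about 0.13. The contribution of each score's own T0 value is not sized here, because the article gives no correlation between T0 and T2.

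**What to change.** 1. In Table 2, move CRIq out of the secondary outcomes to a baseline-characteristics row, so that the table agrees with Outcomes Measures.
2. In Statistical Analyses, make clear that CRIq is not among the measures tested for change between arms.
3. Replace the unadjusted independent-samples test of the cognitive scores with a prespecified between-arm comparison at T2, adjusted for the score's own T0 value and with CRIq as an additional covariate. State in advance what will be done for scores that are far from normal, since the present choice of test depends on normality.

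The first two changes are editorial and cost nothing. The third needs no new data, since CRIq and the cognitive scores are already scheduled at T0 before randomisation. CRIq costs one degree of freedom, and each score's own T0 value costs another. If an analysis plan already specifies this model, only the first two changes and a matching sentence in the article are needed.

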### Tele-Rehabilitation Program

On the basis of literature, the present protocol is designed aiming at affecting patients' on different domains in line with a holistic approach to promote well-being: cognition, motor skills, and social environment. The cognitive module integrates a collection of brain training exercises from BrainHQ, a third-party platform developed by Posit Science, that makes available Serious Games (SGs) for multidomain stimulation. The proposed SGs are adaptive type, i.e., the difficulty varies in relation to the user performance and becomes more demanding through both reductions in stimulus display duration and increases in task complexity. Difficulty is maintained immediately over the user comfort threshold, which according to several studies, efficaciously stimulates the neural plasticity (44–46). Cognitive activities are meant to reinforce attention, brain speed, memory, people skills, intelligence, and navigation. The physical module includes a training program of APA exercises (16), delivered through a guided video. Regular participation in an APA exercise program has been previously associated with improved self-rated health and improved mood (47). The proposed exercises aim to train trunk, upper, and lower limbs and are designed to require only: a chair, a gym-stick, two small bottles of water and a resistance band, to be performed. Each module comprises a warming-up, a strengthening and a stretching session, with a level of difficulty (basic and advanced) adjusted according to participants' training level and physical capabilities (e.g., participants with reduced ability in mobilizing the upper limbs may have a customized program comprising advanced/basic exercises only for the lower limbs and vice versa). Social level is addressed with the involvement of caregivers and patients in some leisure activities. The caregiver module includes suggestions of social activities to be carried out with the caregiver during the weekend, such as watching a movie, gardening, cooking etc. At the beginning and at the end of daily activity, participants are asked to fill a questionnaire on their self-perceived physical/emotional status.

### GOAL-App Architecture

A web-application, named GOAL-App, has been specifically designed to implement a weekly tele-rehabilitation program consisting of combined cognitive, physical and social activities (to be performed with the caregiver), according to the clinician indications. Scheduling and monitoring of activities are accessible by the GOAL-App administrator (Figure 2). Each activity is implemented in the three independent modules on cognition, motor skills and social level. The first realized web-app prototype was developed further through a series of design and feedback loops with MCI specialists, patients living with MCI and VCI and their caregivers. Thanks to this participatory design the following critical aspects emerged and were addressed:
- The need for a full screen interface with a few number of large buttons;- The possibility to pause the physical module to take breaks during the exercises, if needed;- The need for a user-manual and a Support Service Center for technical problems.

**Figure 2 F2:**
[figure not shown]
WebApp interface and its functional architecture.

Patients, provided with a tablet, will access the final version of the tele-rehabilitation program through the GOAL-App. Before the beginning of the treatment, participants will be trained to use the tablet autonomously at their home. During the training sessions participants, with the support of their caregivers, will go through each module of the program, at least once, until they feel familiar with the use of the device. A mobile wifi router will be provided in case participants don't have access to internet connection. In addition, they will be given a kit, made up of a stick and a resistance band, to perform the physical exercises at home.

### Outcomes Measures

As the aim of this program will be to involve the participants in multidimensional activities to counteract cognitive decline, the primary outcome of this study will be the changes of cognitive domains evaluated (such as general cognitive assessment, memory, attention, and executive functions, visuospatial/constructional ability, and language) of the whole sample through a comprehensive neuropsychological assessment at T_0 and at T_2 (see Table 2 for a detailed list of the used neuropsychological tools). Together with the cognitive level, the following secondary outcomes will be evaluated in the whole sample at T_0 and T_2: independence, presence of depressive symptoms, quality of life and physical activity level through scales and actigraphic data (see Table 2 for the used questionnaires). In addition, the primary and secondary outcomes will be evaluated in the treatment group before and after the tele-rehabilitation program using a reduced battery of tests (see Table 2).

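### The primary outcome is a ten-row cognitive battery judged against one 0.05 threshold, with no single endpoint, composite, testing order, adjustment or success rule

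*Protocol article*

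**What the plan says.** Under Outcomes Measures, the protocol article says that "the primary outcome of this study will be the changes of cognitive domains evaluated". It names these as "general cognitive assessment, memory, attention, and executive functions, visuospatial/constructional ability, and language", to be assessed "of the whole sample through a comprehensive neuropsychological assessment at T_0 and at T_2", and refers to Table 2 for the instruments.

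Table 2 lists ten rows under "PRIMARY OUTCOME": MoCA, digit and Corsi spans, FCSRT, Rey figure recall, modified card sorting, Trail Making, Stroop, Rey figure copy, semantic fluency and phonemic fluency. They are grouped under the five domains, and all ten are ticked at T0 and T2. Two rows hold more than one score. The span row reads "The Digit span and the Corsi span tasks (backward and forward", which is four scores. Participants' Evaluation describes the FCSRT as "Delayed Free Recall (DFR) and Immediate Free Recall (IFR) for verbal episodic memory evaluation", which is two.

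The Statistical Analyses section says that "a statistical test for independent samples will be performed to look at significant changes in primary and secondary outcome measures between control and treatment groups" and sets one rule: "An alpha level of ≤ 0.05 will be considered as significant".

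The Sample Size section reports power above 70% with 60 subjects at α = 0.05. It refers to primary outcome scores in the plural, without saying which one and without an effect size or standard deviation.

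**The concern.** The protocol makes several measures primary and gives each the whole of alpha, yet has no rule for turning their results into one conclusion. A trial with one significant row and nine null rows could be reported as meeting its primary outcome, and nothing in the text would contradict that. The 0.05 level is then the error rate of each test and not of the efficacy conclusion, which the Abstract says the results will inform.

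The power statement has the matching problem. Power above 70% can be true of one comparison at 0.05, but the protocol does not say which. If alpha were later divided over the battery, the stated power would no longer hold.

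**Working it through.** **1. Inputs**
- From the document: ten primary rows and five domains (Table 2); 0.05 per test (Statistical Analyses); 60 subjects and power above 70% (Sample Size).
- Assumed, because not stated: two-sided tests, 30 per arm, and equal correlation ρ between every pair of tests, taken from 0 to 0.8.
- Also assumed: any one significant result is read as success.

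**2. Number of scores named in the text**

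Ten rows + 3 extra span scores + 1 extra FCSRT score = 14.

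**3. The plan's own power figure**

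It cannot be reproduced, because no effect size or standard deviation is given. Working backwards, 70% power at 30 per arm and two-sided 0.05 corresponds to a standardised difference of d = 0.65 (t-based).

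**4. Chance of at least one p ≤ 0.05 under no effect**

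For independent tests the formula is 1 − 0.95^k:
- k = 5: 1 − 0.7738 = 22.6%
- k = 10: 1 − 0.5987 = 40.1%
- k = 14: 1 − 0.4877 = 51.2%

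For correlated tests it is 1 − ∫ P(|Z| < 1.96 given common factor t)^k φ(t) dt, with an equicorrelated normal model:

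| Tests | ρ = 0 | 0.3 | 0.5 | 0.7 | 0.8 |
|---|---|---|---|---|---|
| 5 domain scores | 22.6% | 20.9% | 18.3% | 14.8% | 12.7% |
| 10 rows | 40.1% | 35.1% | 28.7% | 21.3% | 17.3% |
| 14 named scores | 51.2% | 43.8% | 34.8% | 24.9% | 19.7% |

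**5. Counting only results that favour treatment (nominal 2.5%)**

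For ten independent tests, 1 − 0.975^10 = 1 − 0.7763 = 22.4%. This falls to 14.4% at ρ = 0.5 and 8.6% at ρ = 0.8. For five tests the range is 11.9% (ρ = 0) to 6.4% (ρ = 0.8).

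**6. What splitting alpha would cost**

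Bonferroni over ten rows gives 0.05/10 = 0.005 per test. At d = 0.65 and 30 per arm, power for one test falls from 70% to about 36%. Restoring 70% would need about 55 per arm (110 in total) before dropout. Holm begins at the same 0.005 and relaxes only after a rejection.

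**7. What a composite would do**

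The composite is the mean of ten standardised scores, with ρ = 0.5 and d = 0.5 on each affected test (both assumed). Its standard deviation is √((1 + 9 × 0.5)/10) = √0.55 = 0.742. Its effect is d = 0.5 × (share of tests affected)/0.742.

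| Tests affected | Composite d | Power, 30 per arm |
|---|---|---|
| 10 of 10 | 0.67 | 73% |
| 5 of 10 | 0.34 | 25% |
| 3 of 10 | 0.20 | 12% |

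A single affected test with d = 0.5 has 48% power at 0.05.

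**The case against.** **Multiplicity detail is often left to an analysis plan, and none is shown here.** This stands as far as the choice of method goes. It does not remove the point, because the protocol itself fixes a multiple primary outcome, one threshold, and a sample size at the full 0.05. An unseen plan that split alpha would undercut the stated power, and one that named a single endpoint would change the stated primary outcome. That each measure is tested at 0.05 is an inference, though it is the natural reading.

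**The primary outcome may be five domains and not ten tests.** The Outcomes Measures wording allows this. No domain score is defined, however, and the inflation remains at 13% to 23%.

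**A reader might quote 29% to 40% as the false-claim rate.** The document does not support that as a fixed figure. It gives no correlations, and stopping at ρ = 0.5 is a choice; at 0.7 to 0.8 the rate is 17% to 21%. The range also counts significance in either direction, and a result favouring control is not an efficacy claim.

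**A reader might count about 16 scores** by splitting Trail Making and Stroop in two. The text names each as one test, so only 14 scores are documented.

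**A reader might see a composite as a free gain.** It gains only if the effect is spread over most of the battery; at five of ten tests or fewer it does worse than one affected test taken alone.

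**Conclusion.** The point holds and should be corrected before analysis. The protocol article makes ten test rows in five domains primary, applies one 0.05 threshold, and names no deciding endpoint, composite, order, adjustment or success rule. Its power above 70% is attached to no identified score.

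The size of the inflation depends on assumptions. If any one significant row is read as success, which the document neither says nor excludes, the error rate is roughly 17% to 40% for ten two-sided tests. It is about 9% to 22% against 2.5% in the favourable direction only, and about 13% to 23% for five domain scores. All these ranges run over assumed common correlations of 0.8 to 0. Every scenario is at least about two and a half times nominal. Secondary outcomes and the paired tests within the treatment arm are not counted.

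**What to change.** Before outcome data are examined by arm, do one of the following:
- Name one primary endpoint based on T0-to-T2 change. Examples are the change in MoCA, or the change in a global cognitive composite whose component scores, direction and standardisation are defined in advance.
- Keep the battery as a set of primary outcomes, list the exact scores, and state a multiplicity procedure such as Holm together with the rule for declaring success.

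If one endpoint is chosen, make the remaining tests secondary, reported as estimates with confidence intervals and no efficacy claim. In either case, say in the Sample Size section which endpoint the power above 70% refers to, with its effect size and standard deviation.

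Naming one endpoint costs only wording, because all ten rows are already collected at T0 and T2. Success could no longer be claimed on any single test, and a composite loses power if the effect is confined to a few domains. Keeping the battery costs power at 60 subjects, as the 0.005 calculation shows.
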